## Abstract

Cognitive reappraisal (CR) is one of the core treatment components of cognitive behavioral therapy (CBT) and is the gold standard treatment for major depressive disorders. Accumulating evidence indicates that cognitive reappraisal could function as a protective factor of cognitive vulnerability to depression. However, the neural mechanism by which CR training reduces cognitive vulnerability to depression is unclear. There is ample evidence that the prefrontal–amygdala circuit is involved in CR. This study proposes a novel cognitive bias model of CR training which hypothesizes that CR training may improve the generation ability of CR with altered prefrontal–amygdala functional activation/connectivity, thus reducing negative cognitive bias (negative attention bias, negative memory bias, negative interpretation bias, and/or negative rumination bias) and alleviating depressive symptoms. This study aims to (1) explore whether there is abnormal CR strategy generation ability in individuals who are cognitively vulnerable to depression; (2) test the hypothesis that CR training alleviates depressive symptoms through the mediators of cognitive bias (interpretation bias and/or rumination bias); (3) explore the neural mechanism by which CR training may enhance the ability of CR strategy generation; and (4) examine the short- and long-term effects of CR training on the reduction in depressive symptoms in individuals who are cognitively vulnerable to depression following intervention and 6 months later. The study is promising, providing theoretical and practical evidence for the early intervention of depression-vulnerable individuals.

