On the other hand, the frequent user of CR showed stronger downregulation of amygdala activation to negative emotion stimuli (Kanske et al., 2012), and CR in healthy individuals can attenuate the excitatory connectivity from the dlPFC to the inferior frontal gyrus (IFG) and increase the inhibitory connectivity from the IFG to the dlPFC, which supports the selection of appropriate alternative CR strategies (reinterpretations) in the IFG, and afterward, inhibition of original interpretations maintained and monitored in the dlPFC (Morawetz et al., 2016). Neurofeedback-guided CR training targeting the left vlPFC improved the frequency of CR strategy use (indexed with ERQ) as well as depression symptoms (Keller et al., 2021). Therefore, CR training may enhance CR ability by changing the functional activity/connectivity pattern of prefrontal-amygdala circuits, which then alleviates cognitive biases and thus depressive symptoms.

Researchers suggested that specific measures using lab-based tasks may be more sensitive to detect training effects (Cohen and Ochsner, 2018). Therefore, in this study, we will combine the RIT, CR training, and fMRI, as well as self-report measures (cognitive/emotion/symptoms) to address the following aims: (1) to examine whether the CR ability (reappraisal inventiveness) of the population with cognitive vulnerability to depression is abnormal; (2) to test the hypothesis that CR training alleviates depressive symptoms through the mediators of cognitive bias (e.g., interpretation bias and/or rumination bias); (3) to investigate the neural substrates (structural/functional) of prefrontal–amygdala circuits through which CR training improves the ability to generate a CR strategy; and (4) to examine the short- and/or long-term effects of CR training on reducing depression symptoms in cognitively vulnerable individuals immediately after intervention and/or 6 months to provide theoretical and practical evidence for early intervention in these populations. We postulate that CR training improves CR ability (RIT) by changing the brain activity/function connectivity of the prefrontal-amygdala circuits, thereby reducing negative cognitive biases (NCPBQ-NIB, NCPBQ-NRB, and CSQ) and improving depression symptoms (CESD) (Figure 1).

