### Statistical analysis

#### Behavioral and self-report data

##### Intervention effect analysis

A 3 (group: CR = cognitively vulnerable intervention subgroup; WC = cognitively vulnerable waiting-list control subgroup; NC = normal control group) × 3 (time point: T_0_ = pretraining, T_1_ = post-training, T_2_ = 6-month follow-up) mixed design will be adopted. Using the HLM analysis, as well as mediating/modulating effect analyses, we will investigate (1) hypothesis 1, whether the changes in negative cognitive biases and depressive symptoms across time 1 and time 2 differ significantly among groups and (2) hypothesis 2, whether the changes in negative cognitive bias (negative interpretation bias and/or negative rumination bias) pre- and post-training could predict depression symptoms at T_1_ and/or T_2_.

To test hypothesis 1, we will conduct an HLM analysis with time (0 = pretraining; 1 = post-training), group (0 = CR; 1 = WC; 2 = NC), and the interaction between time and group as predictor variables and the with CESD score as the outcome variable. To test hypothesis 2, we will conduct mediating/modulating effect analyses among CR ability (RIT) and tendency (ERQ), negative cognitive bias (NCPBQ), cognitive vulnerability (CSQ), and depressive symptoms (CESD) at T_1_ and/or T_2_. The HLM and mediating/modulating effect analyses will be conducted in SPSS (Statistical Product and Service Solutions) software version 22.0 (SPSS, Inc., Chicago, IL, United States) combined with the PROCESS Macro (Hayes, 2012).

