## Limitations

First, we include the process measures of cognitive bias (negative interpretation bias and/or negative rumination bias) to evaluate the intervention effects, which should be interpreted as exploratory. More solid progress will depend on a systematic examination of the neural network mechanism involved in CR training effectiveness. The neural signature of the cognitive control and emotion regulation network during CR, such as global metrics and topological characteristics (Pan et al., 2018), is needed. However, connectome-based predictive modeling of distributed neural networks during CR has not revealed a meaningful whole-brain signature of CR tendency (Pan et al., 2018; Burr et al., 2020). Therefore, more evidence is needed to explore the neural network mechanism of CR training, which may provide more perspectives on the neural and cognitive targets of CR training.

Second, evidence of both clinical effectiveness and cost effectiveness of CR training is necessary for future studies to test the feasibility of CR training in primary care, as well as in clinical settings for vulnerable individuals with depression, and generalize CR training to those populations that may benefit from training. Therefore, various context-specific CR training programs should be forged into well-specified protocols that could be tested in randomized controlled trials to provide such evidence. Furthermore, further studies comparing CR training with other components of CBT as well as its whole package are warranted to assess its cost-effectiveness.

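### Hypothesis 2 can be supported by either of two bias scales at either of two time points, and the article disagrees with itself on which bias scales count and whether the results are exploratory

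*Protocol article*

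**What the plan says.** The article describes the bias hypotheses in several places.

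- **Abstract.** The conceptual model speaks of "reducing negative cognitive bias (negative attention bias, negative memory bias, negative interpretation bias, and/or negative rumination bias", which is four biases. Aim 2 in the same paragraph names only interpretation and/or rumination bias, and is worded as a hypothesis to be tested.
- **Introduction, last paragraph.** Aim 2 is again a hypothesis to be tested. The postulated chain ends in "reducing negative cognitive biases (NCPBQ-NIB, NCPBQ-NRB, and CSQ) and improving depression symptoms (CESD"), so CSQ is now one of the biases.
- **Secondary outcomes.** CSQ and the NCPBQ both stand under the negative cognitive bias heading. The NCPBQ description assigns the NIB and NRB subscales to the mediation analyses.
- **Intervention effect analysis, hypothesis 1.** It asks "whether the changes in negative cognitive biases and depressive symptoms across time 1 and time 2 differ significantly among groups". The one model given for it is a time-by-group hierarchical linear model with CESD as outcome.
- **Intervention effect analysis, hypothesis 2.** It asks "whether the changes in negative cognitive bias (negative interpretation bias and/or negative rumination bias) pre- and post-training could predict depression symptoms" at T1 and/or T2. Its analysis relates reappraisal ability and tendency to "negative cognitive bias (NCPBQ), cognitive vulnerability (CSQ), and depressive symptoms (CESD) at T_1_ and/or T_2". There the NCPBQ has no subscale named and CSQ is a separate construct.
- **Neuroimaging data analysis, functional connectivity.** Cognitive bias is written as CSQ/NCPBQ and enters path analyses meant to verify the cognitive bias model.
- **Limitations.** The bias process measures are included "to evaluate the intervention effects, which should be interpreted as exploratory".

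**The concern.** Mediation through cognitive bias is aim 2 and is the claim the Conclusion carries. As written, hypothesis 2 offers four ways to succeed (two scales by two visits), with no order among them and no statement of which decides. A reader who takes the scale list from the Introduction, or the whole NCPBQ from the analysis paragraph, has more. A pattern of NIB only, NRB only, T1 only or T2 only could each be presented as support, so the hypothesis is hard to refute and its error rate exceeds that of a single test.

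Two further gaps add to this. The bias half of hypothesis 1 has no model and no named scale. The status of all these results also depends on the section read: exploratory in one, a test or verification in others.

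**Working it through.** **1. The sections side by side**

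| Place | Scales counted as bias | Status |
|---|---|---|
| Abstract, conceptual model | four NCPBQ biases | hypothesised model |
| Abstract, aim 2 | interpretation and/or rumination | test |
| Introduction, aims and postulate | interpretation and/or rumination as examples in aim 2; NIB, NRB and CSQ in the postulate | test |
| NCPBQ description | NIB, NRB (for mediation) | secondary outcome |
| Hypothesis 2, statement | NIB and/or NRB | hypothesis |
| Hypothesis 2, analysis | NCPBQ, with CSQ alongside | mediating/modulating analysis |
| Path analyses | CSQ/NCPBQ | verify |
| Limitations | interpretation and/or rumination | exploratory |

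The pair NIB and NRB is the best-supported set. The Introduction's postulate, the hypothesis 2 analysis and the path analyses do not match it.

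**2. Inputs for the error rate**

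- The article states no error rate for these hypotheses, so there is none to reproduce. Its only related figure is the sample size: 75 per group, d printed as 0.0.39 (read as 0.39), 65% power. A two-sided 5% t-test gives 66.0%, so that figure holds. It supplies n = 150 and 0.39 for step 5.
- Level: two-sided 5% per test (assumed; not stated).
- Correlation between test statistics: 0 to 0.7 (assumed; not stated).

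**3. Prediction tests, two scales, one visit**

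With independent tests, the chance of at least one false positive is 1 − (1 − 0.05)² = 1 − 0.9025 = 9.75%. With correlated tests it is 1 − P(|Z1| ≤ 1.96 and |Z2| ≤ 1.96):

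- correlation 0.5: 9.1%
- correlation 0.7: 8.3%

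**4. Prediction tests, two scales, two visits**

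Independent: 1 − 0.95⁴ = 1 − 0.8145 = 18.5%. By simulation from a multivariate normal, with the same correlation between scales and between visits:

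- 0.5: 16.2%
- 0.7: 13.6%

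**5. Indirect effects, either of two mediators, one visit**

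An indirect effect is declared only if both paths (training to scale, scale to symptoms) are significant at 5%. Suppose there is no true scale-to-symptom path, n = 150, and the scales correlate 0.5.

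| Training effect on both scales (assumed) | One mediator | Either of two |
|---|---|---|
| none | about 0.25% (0.05 × 0.05) | about 0.5% |
| 0.39 SD | 3.4% | 6.2% |
| 0.8 SD | 5.2% | 9.1% |

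The inflation therefore appears when training does move the scales but the scales do not drive symptoms. That is the situation a mediation study has to recognise.

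**6. Check of the remedy**

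Under Holm with two scales at one visit, the smaller p-value must be below 0.05/2 = 0.025. With independent tests the any-one error is 1 − 0.975² = 4.94%.

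**The case against.** A fair defence has four parts.

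- **The mediator pair is fixed.** The NCPBQ description, the statement of hypothesis 2 and aim 2 in the Abstract all give interpretation and rumination bias. A reader might infer from the Abstract's four-bias list that any of four or five scales will do, and so that chance confirmation runs at up to four times 5%. The documents do not support that. The list describes a conceptual model, and the hypothesis 2 analysis treats CSQ as vulnerability, apart from bias. The scale choice alone supports about twice 5% at most.
- **No sentence says one significant scale is enough.** The either/or wording sits inside a question to be investigated. This is true, but no sentence says which scale or visit decides, and the literal reading admits any of them. It applies only to hypothesis 2 and the mediation aim. Hypothesis 1 has no such wording; its defect is the missing bias model.
- **The bias scales are secondary and called exploratory, and alpha and multiplicity rules may sit in an analysis plan not shown.** The absence of an adjustment is therefore not the point. The point is that the article uses inconsistent scale sets and two incompatible descriptions of status, which an unseen plan does not reconcile.
- **Mediation tests are conservative.** This stands when training barely moves the scales (step 5). It does not cover hypothesis 2 as worded, which is an ordinary prediction question.

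A reader might also set the Procedure's promise to validate a hypothesis against the exploratory label. That passage concerns improvement in reappraisal inventiveness, not bias, so it is no contradiction here.

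**Conclusion.** The point holds for hypothesis 2 and the mediation aim. The success rule is open over two scales and two visits, the scale set is inconsistent across sections, the status is contradictory, and half of hypothesis 1 lacks a model.

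For the prediction tests, at an assumed two-sided 5% each, the chance of at least one false positive is about 8–10% for two scales over correlations 0 to 0.7. If both visits count it is about 16–18% for correlations up to 0.5, falling to 13.6% at 0.7. For indirect effects at one visit it ranges from under 1% to about 9%; the top of that range rests on an assumed training effect of 0.8 SD on both scales. None of this touches CESD as the scale under the primary outcome heading.

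**What to change.** Either of two repairs would do.

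**A. Keep a test of the bias hypothesis.**

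- Use NIB and NRB as the bias set in the Introduction, the Intervention effect analysis and the path analyses.
- Name one deciding time point for hypothesis 2.
- Test the two scales there under Holm, or pre-name one mediation model with one deciding effect. That model should fit the protocol's theory, which the Introduction sets out as serial (interpretation bias, then rumination, then symptoms), so a parallel total effect is not the obvious choice.
- For hypothesis 1, let CESD come first, then fit the same time-by-group model to NIB and NRB under Holm.
- Label CSQ, attention bias, memory bias and the other time point exploratory.
- Limit the exploratory statement in the Limitations to those items.

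**B. Keep the Limitations as they stand.** Call all bias results exploratory, and change the wording about testing (Abstract, Introduction) and verifying (path analyses) to match. The scale set should still be made consistent.

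The cost is wording. The named software already fits these models and no new data are needed. The article says no participant had been recruited at submission, so at that point the change could have preceded all results. The downside of A is that the smaller of the two p-values must reach 0.025 rather than 0.05. The downside of B is that the trial can no longer claim to have tested its mechanism.

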## Methods

Using RIT and CR training in combination with fMRI, we will explore (1) the deficits in CR ability (indexed with RIT) for the depression-vulnerable group; (2) the short- and long-term antidepressant effects of CR training on depression-vulnerable populations; (3) whether it is feasible to reduce negative cognitive biases (negative interpretation bias and/or negative rumination bias) and depressive symptoms of depression by improving reappraisal inventiveness; and (4) the changes in the prefrontal–amygdala circuit induced by CR training, including changes in the functional activation and connectivity of the regions of interest (prefrontal cortex and amygdala) before and shortly after CR training and changes in the volumes of these regions of interest (prefrontal cortex and amygdala) long after CR training (6 months later) (Figure 2).

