##### Negative cognitive processing bias questionnaire

The negative cognitive processing bias questionnaire (NCPBQ) contains 4 dimensions, i.e., negative attention bias (NAB), negative memory bias (NMB), negative interpretation bias (NIB), and negative rumination bias (NRB), using a Likert 4-point scale from 1 (completely disagree) to 4 (completely agree). The NCPBQ has good internal reliability (Cronbach’s alpha coefficient = 0.89), split-half reliability (*r* = 0.87), construct validity for a four-factor model that explained 50.152% of the total variation (CFI = 0.92, RMSEA = 0.05), and criterion validity coefficients of 0.395 (relative to the Beck Depression Self-Rating Scale) and 0.548 (relative to the Dysfunctional Attitude Questionnaire) (Yan et al., 2017). The negative interpretation bias (NIB) and the negative rumination bias (NRB) subscales will be utilized in the mediation analyses.

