##### Data analysis

(1) Analysis of the morphological characteristics of brain structure: Voxel-based morphometry (VBM) will be adopted to calculate the concentration and volume of each voxel in different brain tissues (gray matter, white matter, and cerebrospinal fluid) using templates for the whole brain and different brain tissues created based on 3D data, and the volumes of ROIs will be compared between different groups to examine (1) whether the volumes of ROIs before and after CR training differ significantly and (2) if the volumes of ROIs differ significantly, whether the changes in the volumes of the ROIs can predict depressive symptoms immediately after training (T_1_) or 6 months later (T_2_).

(2) Region of interest analysis: The anatomical localization of functional images will be determined with reference to the anatomical maps of the brain in Talairach coordinates and based on the opinions of experienced neuroimagers. Using MARSbar software, the prefrontal subregions (dlPFC/dmPFC/vlPFC/vmPFC) and the amygdala will be extracted as BOLD signals of ROIs by subtraction between the baseline and CR (±) conditions. The data will then be exported to SPSS for statistical processing, in which the activation of the region of interest will be used as a predictor of depressive symptom scores to investigate (1) whether the activation levels of regions of interest (prefrontal lobe and the amygdala and its subregions) before and after CR training differ significantly and (2) if the activation levels do differ significantly, whether the changes in the activation levels of the regions of interest can predict depressive symptoms (T_1_ and T_2_).

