(3) Functional connectivity analysis: Taking the amygdala as the seed point and the average time series within the seed point as the reference time series, we will perform “one point to multipoint” linear correlation analysis with the time series of each ROI. Using the average signals of head movement, the white matter, the cerebrospinal fluid, and the whole brain as covariates and using the prefrontal-amygdala FCs as predictors of depressive symptom scores, we will use between-group *t*-tests, combined with correlation analyses and path analyses, to examine (1) whether the FCs between the prefrontal subregions (dlPFC/vlPFC/dmPFC/vmPFC) and the amygdala before and after CR training differ significantly and (2) if the prefrontal-amygdala FCs do differ significantly, whether the FCs could predict depressive symptoms (T_1_ and T_2_). The FCs between ROIs, cognitive bias (CSQ/NCPBQ), CR ability (RIT), and tendency (ERQ) will then be entered into path analyses to verify the cognitive bias model of CR training.

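### Hypothesis 2 and the ROI volume and activation tests pair a pre-to-post change with the follow-up CESD level and name no T0 CESD, which pulls the bias-to-CESD link downward

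*Protocol article*

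**What the plan says.** In the protocol article, under Intervention effect analysis, hypothesis 2 asks whether changes in bias "pre- and post-training could predict depression symptoms at T_1_ and/or T_2". The mediating/modulating analyses for it list CR ability and tendency, NCPBQ, "cognitive vulnerability (CSQ), and depressive symptoms (CESD) at T_1_ and/or T_2". Pretraining CESD is used explicitly only for hypothesis 1, through the time factor of the HLM.

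Under Data analysis (neuroimaging), two tests follow the same pattern:
- Morphology: "whether the changes in the volumes of the ROIs can predict depressive symptoms immediately after training (T_1_) or 6 months later (T_2".
- Activation: "whether the changes in the activation levels of the regions of interest can predict depressive symptoms (T_1_ and T_2".

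The connectivity test is worded differently: "if the prefrontal-amygdala FCs do differ significantly, whether the FCs could predict depressive symptoms (T_1_ and T_2". Its predictor is the connectivity itself and is not stated as a change.

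Aim 2, in the Abstract and at the end of the Introduction, is that training alleviates depressive symptoms by way of cognitive bias. Limitations calls the bias process measures exploratory.

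**The concern.** Alleviation is a change from T0. A T1 or T2 CESD level partly reflects who was less depressed before training began. Setting a change score against that level mixes two things: whether a fall in bias goes with a fall in symptoms, and whether people whose bias falls most were more depressed at the start.

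The second works against the first. Bias is not perfectly stable, so those highest at T0 fall most on average. Bias and depression are positively correlated, so the same people tend to have higher CESD at T0, and CESD carries over to T1. A real link between improvement in bias and improvement in symptoms would then look weaker than it is. Aim 2 and the Conclusion rest on that link.

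**Working it through.** **The plan's own figure.** The only power statement is 75 per group, d = 0.39 (printed with a typographical slip) and 65% power. At two-sided 0.05 (assumed), 75 per group gives 0.666 by the normal approximation and 0.660 by the noncentral t. Also 150/0.80 = 187.5, so 188. Both reproduce, but neither concerns hypothesis 2, for which the document gives no figure.

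**Inputs**
- c, the T0 correlation of bias and CESD: 0.395. The NCPBQ section reports "criterion validity coefficients of 0.395 (relative to the Beck Depression Self-Rating Scale"; using it for NIB or NRB against CESD is an assumption.
- r, the stability of bias: 0.59. This is the 8-week CSQ retest figure; none is given for the NCPBQ.
- s, the stability of CESD: 0.6, assumed. The document gives none.
- 75 per arm (CR and WC), unit variances within arm.

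**Model.** D = T1 bias minus T0 bias, and CESD1 = s × CESD0 + b × D + error. A positive b means that a larger fall in bias goes with lower CESD.

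Within arm:
- var(D) = 2(1 − r) = 2 × 0.41 = 0.82
- cov(D, CESD0) = c × r − c = −0.395 × 0.41 = −0.162
- corr(D, CESD0) = −0.162/√0.82 = −0.18

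Leaving out CESD0 shifts the slope by s × cov(D, CESD0)/var(D) = −s × c/2 = −0.6 × 0.395/2 = −0.12. In this model the shift does not depend on r.

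| True slope b | Slope without T0 CESD | Slope with T0 CESD |
|---|---|---|
| 0.30 | 0.30 − 0.12 = 0.18 | 0.30 |
| 0.15 | 0.15 − 0.12 = 0.03 | 0.15 |
| 0 | −0.12 | 0 |

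**Simulation** (75 per arm, arm in every model). It reproduces these slopes.
- b = 0.30: power about 50% without T0 CESD and 98% with it.
- b = 0.15: about 6% without, 53% with T0 CESD, and 45% with T0 CESD and T0 bias.
- b = 0: a significant wrong-sign result in about 26% of runs without T0 CESD.

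Adding T0 CESD, with or without T0 bias, recovers the true slope.

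**Sensitivity to c.** For c from 0.20 to 0.55, a true slope of 0.30 appears as 0.30 − 0.06 = 0.24 down to 0.30 − 0.165 = 0.135. With b = 0, c = 0.20 and r = 0.59, the unadjusted correlation is 0.6 × (−0.20 × 0.41/√0.82) = −0.054. By Fisher z at n = 150 that is rejected about 10% of the time. Across s of 0.5-0.7 and r of 0.59-0.82 the figure is about 7-12%.

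**Sensitivity to the model.** Suppose instead that the concurrent correlation stays at 0.395 at T1 and the lagged one is 0.395 × 0.59 = 0.233. The unadjusted correlation of D with CESD1 is then (0.395 − 0.233)/√0.82 = +0.18, which is the right sign. Partialling T0 CESD gives (0.18 + 0.6 × 0.18)/√((1 − 0.18²)(1 − 0.6²)) = 0.288/0.787, about 0.37. The sign holds, but the link is roughly halved.

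**Change-on-change.** Using CESD change as outcome shifts the slope by −s × c/2 + c/2 = c(1 − s)/2 = 0.395 × 0.4/2 = +0.08. It errs in the other direction, so it does not suffice alone.

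**Brain measures.** The document gives no correlation of ROI volume or activation with CESD and no retest value, so c and r are unknown. Methods also places the volume change "long after CR training (6 months later", so it need not run from T0 to T1.

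**The case against.** The strongest objection is that this rests on silence. Nothing says that T0 CESD will be left out. The article condenses a fuller plan, the phrase about T1 and/or T2 may only fix the timing of the outcome, and the design has three time points. That stands as far as it goes: a reader might infer that the sponsor has decided to omit T0 CESD, and the document does not support that. What remains is that the question itself is posed as change against level, which does not match the aim.

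Three stronger readings are tempting and should not be drawn.
- **All imaging prediction tests are affected.** The connectivity test uses connectivity values not stated as a change, so this argument does not cover it. For volume and activation the mismatch is on the page, but its effect cannot be signed or sized.
- **The sign will be wrong.** Reversal needs a weak or null link, or a bias SD that shrinks after training. With the concurrent correlation held at 0.395 the unadjusted correlation is positive.
- **The training effect is biased.** Randomisation protects the CR-WC comparisons of bias and of CESD. Only the path from bias (or brain measure) to CESD is touched.

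It is also fair that the inputs are borrowed. The 0.395 is whole-NCPBQ against another depression scale. Selection on CSQ and exclusion of depression may narrow the spread of T0 CESD and lower the correlation. The exploratory label on the bias measures limits the weight of the point.

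**Conclusion.** The point holds for hypothesis 2. As worded, the test relates change in bias to follow-up CESD level, and for the questionnaire measures this pulls the path downward. Attenuation is the general result. A shift of about −0.12 in the standardised slope follows from c = 0.395 and s = 0.6, and about −0.06 from c = 0.20. The power and wrong-sign percentages illustrate those assumptions and are not predictions for this trial.

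For ROI volume and activation the same mismatch is present with unknown consequence. Connectivity, hypothesis 1 and the randomised effects are outside the point. It should be corrected because the mediating role of bias is a stated aim, the values needed are in the T0 assessment, and the Ethics statement says that nobody had been recruited at submission.

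**What to change.** In the hypothesis 2 models, including those run in PROCESS, and in the ROI volume and activation prediction models:
- keep CESD at T1 or T2 as the outcome;
- add T0 CESD, the T0 value of the predictor (NIB, NRB, ROI volume or activation) and arm as covariates;
- word the question as predicting CESD at T1 or T2 given T0 CESD;
- report CESD change on predictor change as a sensitivity analysis;
- state for volume whether the change runs to T1 or to 6 months.

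The cost is two or three degrees of freedom per model and the loss of participants missing a T0 value. The T0 predictor term also costs some power: in the example at a slope of 0.15, from 53% to 45%, against about 6% unadjusted. With that term in the model, the coefficient on change equals the coefficient on the T1 value of the predictor given its T0 value, and it should be interpreted that way.
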